### Recruitment

Participants will be identified from the list of RT-PCR positive SARS-CoV-2 cases obtained daily from the UC Christus Health Network virology laboratory, COVID-19 outpatient clinics, or the Emergency Rooms. This is a large private, academic health network in Santiago, Chile. Additional patients will be recruited from City Health Departments, local primary care clinics, and through advertising in the community. The recruitment period will continue until the enrollment target is reached.

Cases will be contacted by telephone to explain the study, invite participation, and confirm eligibility. A member of the research team will contact the index case via telephone for a pre-screening discussion (clinical inclusion and exclusion criteria, medical history details and verbal consent). If the participant is eligible to participate, he/she will be provided with a link to an electronic survey, to confirm eligibility and to provide consent to participate. Once an index case has indicated willingness to participate in the study, household contacts will be assessed for eligibility. If at least one household member is considered eligible, he/she will be sent a link to an electronic survey to confirm the reported information. During the recruitment telephone calls, treatment ineligible contacts in each household will be identified and invited to participate in the study.

This pre-consent online approach will reduce face-to-face contact time and the possible exposure of study staff and participants to infection by ensuring all participants are consented and eligibility confirmed, prior to Study Day 1.

### Baseline and follow-up home visits

Refer to Table 2. To maintain isolation of index cases and their household contacts, all biological samples for the study will be collected during home visits. Home visits will be conducted by appropriately trained trial staff. Staff teams will be composed of a physician and a nurse. All will be trained in Good Clinical Practice and study procedures.

**Table 2 Tab2:** Protocol for home-visit procedures and data collection

	Procedures
Day 1	Medical history Brief physical examination Vital signs (forehead temperature, pulse, blood pressure, pulse oximetry) Document weight and height Review baseline symptoms, if applicable Document concomitant medications and therapies Baseline adverse event assessment Saliva sample collection Nasal brushing for transcriptomics Nasal lining fluid sampling for IgA Blood sample collection (2 tbsp; about 30 ml) Dispense and instruct on use of diary cards Dispense individual thermometers for each participant Urine sample collection and pregnancy test pack, if applicable Administer acetaminophen 1000 mg PO pre-medication, if applicable Study drug administration, if applicable Observation for 20 min post study drug administration, if applicable General education to patients and family members about COVID-19 standard care
Day 6	Brief physical examination Vital signs (forehead temperature, pulse, blood pressure, pulse oximetry) prior to study drug administration Review adverse events Review concomitant medications Saliva sample collection (immediately prior to study drug administration) Nasal lining fluid sampling for IgA Blood sample collection (2 tbsp; about 30 mL) Urine sample collection and pregnancy test pack, if applicable Administer acetaminophen 1000 mg PO pre-medication, if applicable Study drug administration, if applicable Collect completed diary cards and dispense new diary cards Observation for 20 min post study drug administration, if applicable
Day 11	Brief physical examination Vital signs (forehead temperature, pulse, blood pressure, pulse oximetry) prior to study drug Review adverse events Review concomitant medications Collect completed diary cards and dispense new diary cards Saliva sample collection (immediately prior to study drug administration) Nasal lining fluid sampling for IgA Blood sample collection (2 tbsp; about 30 ml) Urine sample collection and pregnancy test pack, if applicable Administer acetaminophen 1000 mg PO pre-medication, if applicable Study drug administration, if applicable 12) Observation for 20 min post study drug administration, if applicable
Day 16 & 21 (± 24 h)	Diary completion Saliva sample collection
Day 29 (± 24 h)	Brief physical examination Vital signs (forehead temperature, pulse, blood pressure, pulse oximetry) Review adverse events Review concomitant medications Collect completed diary cards Blood sample collection Saliva sample collection Closure of study

Day 1 procedures must be executed within 72 h of a confirmed COVID-19 index case (RT-PCR evidence of SARS-CoV-2). During the first visit, participants will read and sign an informed consent form available as online appendices. Each household will also be randomized to IFN ß-1a treatment or standard of care. All study participants, regardless of their assignment, will be asked to monitor any symptoms of illness during the trial and, in particular, any ‘flu-like’ symptoms for the first 4–24 h following IFN ß-1a treatment, using an electronic diary. Study participants will be instructed to follow all recommendations from the Ministry of Health and advice from their medical providers in regard to COVID-19 clinical care. If participants are hospitalized during the study, all clinically relevant treatments will be provided as per health guidelines. Consent will be requested for access to medical records relating to any hospitalization or clinic visit.

Participants in the IFN ß-1a treatment arm will be alerted to potential influenza-like symptoms that are sometimes associated with IFN treatment and will be advised to take the provided acetaminophen (1000 mg 4 times per day) from the time of IFN administration until 24 h post-injection, to reduce the likelihood of these symptoms. Participants in the control arm will also be instructed to take the provided acetaminophen within 24 h of the first home visit, to conform with the intervention group. Participants will receive information on the potential risks of IFN ß-1a treatment during pregnancy and other contraindications for PLEGRIDY® use.

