### Primary and secondary objectives

The two co-primary objectives of this study are:To determine whether IFN ß-1a treatment reduces the proportion of infected cases shedding SARS-CoV-2 at day 11 after randomization.To determine whether IFN ß-1a treatment reduces the incidence of SARS-CoV-2 transmission from index cases to treatment-eligible household contacts, as measured by any positive upper airway infection evidenced by real-time Polymerase Chain Reaction (RT-PCR), in contacts at day 11 after randomization.

Secondary objectives of this study are:To determine whether in index cases infected with SARS-CoV-2, IFN ß-1a treatment compared with standard of care reduces the duration of SARS-CoV-2 upper airway virus shedding over 28 days following randomization.To determine whether IFN ß-1a treatment affects the incidence of SARS-CoV-2 upper airway infection or serological conversion by study day 29 in household contacts.To determine whether IFN ß-1a treatment compared with standard of care reduces the proportion of infected cases that require hospital admission or die due to COVID-19.To determine the safety of IFN ß-1a in the treatment and prevention of SARS-CoV-2 infection.

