### Data analyses

Analyses of data for primary and secondary objectives will be conducted per protocol and through intent-to-treat using the procedures detailed below and described in greater detail in a statistical analysis plan, available upon request. Data analysts will be blind to treatment allocation. Analyses will be conducted using R and statistical coding will be available to the public upon request and approval by the investigators.

#### Analysis for primary objective 1

The Primary Objective 1 is to determine whether IFNß-1a treatment reduces the number of COVID-19 cases still shedding SARS-COV-2 in saliva at day 11 following randomization. Statistical analysis of SARS-CoV-2 RT-PCR results from the index case population will be undertaken comparing IFN ß-1a treated index cases to index cases receiving only standard of care. A linear regression model (binomial family, logit link for dichotomous outcomes) will be applied to data collected, where a risk ratio (and 95% confidence interval) will be reported for the treatment arm variable, adjusted for age, sex, baseline viral load and vaccination status at enrollment.

#### Analysis for primary objective 2

The Primary Objective 2 is to determine whether IFN ß-1a treatment reduces the incidence of SARS-CoV-2 transmission from an index case to treatment-eligible household contacts, as measured by upper airway RT-PCR in contacts at day 11 after randomization. Statistical analysis of SARS-CoV-2 RT-PCR results from household contacts will be undertaken comparing households assigned to IFN ß-1a treatment or standard of care. A linear regression model (binomial family, logit link for dichotomous outcomes) with clustering within a household will be applied, where a risk ratio (and 95% confidence interval) will be reported for the treatment arm variable, adjusted for age, sex, baseline viral load of the index case, vaccination status of the index case, vaccination status of eligible contacts, contacts between index case and household contacts during the initial 11-day period, baseline RT-PCR and antibody levels of treatment eligible contacts at enrollment, number of household members and physical details of the household size, e.g. number of bathrooms, number of bedrooms.

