#### Secondary analyses

Additional analysis of both primary objectives will be conducted to include more rigorous group comparisons, e.g. Fisher’s exact test of proportions and a stratified Cochran-Mantel–Haenszel test of proportions. If the primary analysis method, the generalized linear model with binomial family and log link, does not fit the data well, or converge, a logit link will be used, meaning an adjusted odds ratio and 95% confidence interval will be reported. Specifically, a regression model will be used where the outcome variable is Yes/No for SARS-CoV-2 from the day 11 saliva specimen, with odds ratio and 95% confidence interval reported treatment (active/control) variable, following covariate adjustments. Primary objective 2 analysis will include clustering within households, where appropriate. Secondary outcomes will be reported and analyzed as above for the primary outcomes. Poisson and/or ordinal regression analysis will be conducted to compare days of viral shedding between the IFN treated and standard of care groups. The Cox proportional hazards regression model, with similar adjustments for variables as above, will be employed to examine time based, and specifically time-censored, outcome variables between groups. In addition, Bayesian analyses will be estimated using data-generated distributions of viral shedding at days 11, 16, and 29, and household infection rates. These prior distributions will be used to generate posterior probabilities for the intervention arm.

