#### Management of missing data

Information on why individuals chose not to participate or are lost to follow up will be collected. We anticipate few cases of missing data, assuming high adherence among participants and a low drop-out rate. However, to comply with the intent-to-treat analysis, all participants will be included in the data analysis. Hence, we will manage missing data using several strategies. First, if recorded data reports a change of outcome (e.g., change from positive to negative of a SARS-CoV-2 RT-PCR), we would carry forward that finding, as it is very unlikely that the result would change back to positive. Missing data where change has not occurred will be estimated using multiple imputation.

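### Participants who are in hospital or have died by day 11 have no day 11 study sample, and the missing-data rule multiply imputes their PCR outcome without providing for either event

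*Protocol article*

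**What the plan says.** - **Where samples are taken** (Baseline and follow-up home visits): "all biological samples for the study will be collected during home visits". The reason given is to keep index cases and contacts isolated.
- **Co-primary outcome 1** (Data analyses): index cases "still shedding SARS-COV-2 in saliva at day 11 following randomization".
- **Co-primary outcome 2** (Primary and secondary objectives): transmission to contacts, "as measured by any positive upper airway infection evidenced by real-time Polymerase Chain Reaction (RT-PCR), in contacts at day 11 after randomization". The Secondary analyses section, describing the regression for the two primary objectives, says that "the outcome variable is Yes/No for SARS-CoV-2 from the day 11 saliva specimen".
- **Participants in hospital** (Baseline and follow-up home visits): "If participants are hospitalized during the study, all clinically relevant treatments will be provided as per health guidelines". Also: "Consent will be requested for access to medical records relating to any hospitalization or clinic visit". The article gives no rule on endpoint sampling in hospital or on whether a hospital PCR counts.
- **Missing data** (Management of missing data): all participants stay in the intent-to-treat analysis. A recorded change of status is carried forward. For the rest, "Missing data where change has not occurred will be estimated using multiple imputation". Neither hospitalisation nor death is mentioned.
- **Severity as an outcome** (Primary and secondary objectives): a secondary objective asks whether treatment "reduces the proportion of infected cases that require hospital admission or die due to COVID-19".

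**The concern.** The two rules interact. An index case who is positive on day 6 and admitted on day 7 has no day 11 home sample if still in hospital then, and no recorded change, so the outcome is imputed. An index case who dies on day 9 after a positive day 6 sample would be given a shedding status for a day on which none can exist. In both cases the value is missing because the disease progressed, which the trial also measures as an outcome.

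Multiple imputation borrows from participants whose outcome was observed. Under home-only sampling, everyone with an observed day 11 value was at home that day. The observed data therefore cannot show how inpatients were shedding on day 11.

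For contacts the problem is one of definition. A contact who is negative on day 6 and PCR-positive on admission on day 9 is infected if any positive upper-airway result counts. If the outcome is the day 11 saliva specimen, the same contact has a missing value. In an open-label trial this should be settled before the data are analysed.

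**Working it through.** **1. The plan's own figure** (Sample size and power considerations). Inputs: 278 evaluable households, so 278/2 = 139 index cases per arm; 85% v 65% shedding; alpha 0.025; two-sided Fisher's exact test. Exact enumeration gives power of 93.9%, consistent with the stated figure of more than 90%. Drop-out: 278/0.9 = 308.9, that is 309, or 310 as an even total. Contacts: 278 × 3 = 834. These figures agree.

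**2. Assumptions for the sensitivity check.** The article gives no rate of hospitalisation or death by day 11. The range of 5% to 14% is assumed; the upper end is the Background section's share of infections with severe disease, which is not a planning figure for this trial. At 139 per arm it means about 7 to 19 index cases. Two further assumptions: the planning rates, which the article gives for whole arms, apply to home-managed cases; and every inpatient is still shedding.

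**3. Formula.** With hC and hT the shares in hospital on control and on interferon (IFN):

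- shedding proportion per arm = (1 − h) × home rate + h
- true difference = [(1 − hC) × 0.85 + hC] − [(1 − hT) × 0.65 + hT] = 0.20 + 0.15 hC − 0.35 hT
- difference if inpatients are imputed at home rates = 0.20, with risk ratio 0.65/0.85 = 0.765
- overstatement = 0.35 hT − 0.15 hC

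| In hospital, control / IFN | Shedding, control | Shedding, IFN | True difference (points) | Overstatement (points) | Risk ratio |
|---|---|---|---|---|---|
| 5% / 5% | 85.75% | 66.75% | 19.0 | 1.0 | 0.778 |
| 14% / 14% | 87.1% | 69.9% | 17.2 | 2.8 | 0.803 |
| 5% / 10% | 85.75% | 68.5% | 17.25 | 2.75 | 0.799 |
| 10% / 5% | 86.5% | 66.75% | 19.75 | 0.25 | 0.772 |
| 14% / 5% | 87.1% | 66.75% | 20.35 | −0.35 | 0.766 |
| 10% / 2% | 86.5% | 65.7% | 20.8 | −0.8 | 0.760 |

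**4. Direction.** The overstatement is zero when hT = (0.15/0.35) × hC = 0.43 hC. Below that ratio, imputation understates the effect. If home shedding and admission are equal in both arms, the error is zero.

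**5. Sensitivity to the imputation model.** If the model conditions on day 6 status and returns, say, 90% v 80% for inpatients (assumed), the error at equal admission is h × (0.90 − 0.80): 0.5 points at 5% and 1.4 points at 14%, half the values above.

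**6. Power if all inpatients are counted as shedding.** With equal shares: 92.2% at 5%, 90.0% at 10%, 88.0% at 14%. With 5% / 10%: 86.5%. With 10% / 5%: 94.5%.

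**7. Contacts and deaths.** No size can be given. The article states no control attack rate for contacts and no death rate by day 11.

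**The case against.** The strongest reply is that this is detail for the statistical analysis plan, to which the article refers and which is not shown. The imputation model may include hospitalisation and day 6 status, and later home samples (days 16, 21 and 29) can inform survivors who return home. This stands in part: the model is not given, so its results cannot be called wrong. But the sampling location and the missing-data rule are both stated in the article, the latter without exception. Including hospitalisation as a predictor does not create inpatient day 11 values, and later samples do not help for deaths.

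A reader might infer four stronger points that the documents do not support:

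- *All hospitalised participants lack a primary outcome.* A change recorded on day 6 is carried forward, and anyone home again by day 11 can be sampled.
- *They are imputed as if managed at home.* That is one possible model; the article specifies none.
- *Hospital PCR results are excluded.* The article is silent. The contact objective counts any positive, record access is sought, and a positive hospital test could be read as a recorded change to carry forward.
- *The bias favours interferon.* This depends on the balance of admissions and on the assumption that every inpatient still sheds; the table shows it can vanish or reverse.

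Counting every death and inpatient as shedding in the primary analysis would also turn a virological endpoint into a composite that overlaps a secondary objective. That objection stands, so this analysis belongs among the sensitivity analyses.

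**Conclusion.** The concern holds in limited form. Home-only sampling combined with an imputation rule that makes no exceptions leaves hospitalisation and death before day 11 without defined handling in either co-primary outcome. Severity-related missingness is foreseeable here, and the contact outcome can be read two ways when infection is documented only in hospital records.

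The size and direction of any bias are not fixed by the documents. Under the stated assumptions it is an overstatement of 1.0 to 2.8 points on a 20-point difference when admissions are equal. It is close to nil with half as many admissions on interferon, and reversed below about 0.43 of the control rate. No stated figure is wrong. This is a rule to repair before analysis and gives no ground for calling the trial biased towards treatment.

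**What to change.** Amend the missing-data section as follows:

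1. When the day 11 home sample is missing, use a hospital or clinic RT-PCR from the records for which consent is requested before any imputation. For index cases take a result near day 11, within a window fixed in advance; for contacts, any positive up to day 11. Record the specimen type.
2. Include hospitalisation and day 6 PCR status in the imputation model.
3. State how a death before day 11 enters each co-primary outcome. Do not impute a shedding status for deaths under missing at random without such a rule.
4. Report a sensitivity analysis that counts index cases who died, or who were in hospital with COVID-19 on day 11 without a sample, as still shedding.

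The cost is analysis wording plus extraction of PCR results from records. With 251 households enrolled at submission, extraction can be done retrospectively where consent was given, with no change to clinical care. There are two drawbacks. Hospital specimens may not be saliva. Clinical testing may also differ between open-label arms: the Data and safety monitoring section itself warns that interferon side effects could lead to more testing in the treated group.

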**Fig. 2 Fig2:**
[figure not shown]
Household and participant eligibility

**Table 1 Tab1:** Participant inclusion and exclusion criteria

	Inclusion criteria	Exclusion criteria*
Index cases	• Provided a signed and dated informed consent form • Aged 18 to < 80 years of age • Confirmed SARS-CoV-2 diagnosis by PCR within 72 h of first treatment dose • The first known diagnosis in the household • Not currently enrolled in a clinical trial and agree to not take any other investigational treatments over the next 28 days • Must plan to remain resident in the household during the study • Lives in household with at least one other ‘treatment-eligible household contact	• Inability to take medications orally or by injection • Known sensitivity/allergy to interferons or use of interferons for another indication • Known adverse drug-drug interactions with any study drugs • Malignancy • Known clinical immune deficiency • Pregnancy or unwillingness of female participant of childbearing age to use recognized methods of birth control/contraception during the trial period • Retinopathy • Known grade 4 or 5 chronic kidney or liver disease • Known arrhythmias • Known autoimmune disease or chronic inflammatory disease • Chronic liver disease • Hospitalization for depression in the last 3 months • Current suicidal ideation • Previous therapeutic use of IFN
Treatment eligible contact	• Provided a signed and dated informed consent form • Aged 18 to < 80 years of age • Not currently enrolled in a clinical trial and agree to not take any other investigational treatments over the next 28 days • Must plan to remain resident in the household during the study • No history of previously confirmed SARS-CoV-2 diagnosis	
Treatment ineligible contact	• Provided a signed and dated informed consent form, parental informed consent, and assent if applicable • Under 18 years OR ≥ 80 years of age OR aged 18 to < 80 years with any contraindication for IFN treatment listed in ‘exclusion criteria’ • Not currently enrolled in a clinical trial and agree to not take any other investigational treatments over the next 28 days • Must plan to remain resident in the household during the study • No history of previously confirmed SARS-CoV-2 diagnosis	

^*^All household members are ineligible if participation by any member is declined or if the index case has been in complete self-quarantine from other household members during the 48 h prior to diagnosis of SARS-CoV-2 infection

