### Intervention arm

Participants (index cases and treatment eligible household contacts) will receive 125 µg of pegylated IFNß-1a (PLEGRIDY®, Biogen) administered on Study Days 1, 6 and 11 (i.e. for a total of 3 doses). IFN ß-1a will be administered at the home of the participant, via subcutaneous injection from appropriately trained trial staff, for whom administration of subcutaneous injections is within their normal scope of practice (e.g. nurse or physician). The staff will remain at the home for 20 min after the last individual in a household receives their dose of IFN ß-1a, before leaving the residence, to ensure no immediate adverse events associated with IFN administration occur. All field team staff will be supplied with appropriate personal protection equipment, trained in the use of this equipment and in protocols for infection control, and will always attend in pairs. Staff administration of IFN ß-1a will ensure medication adherence.

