### Control arm

Participants randomized to the control group will receive standard of care, including symptom-based supportive treatment provided by the individual’s personal medical provider. This could include acetaminophen, non-steroidal anti-inflammatory drugs, cough suppressants, antibiotics, inhaled bronchodilators. Participants in this arm will not receive any IFN ß-1a treatment or a placebo. This standard of care approach was selected as the comparator, since no other approved intervention medications are available for non-hospitalized cases.

All participants, regardless of their allocation group, will receive a brochure with the recommendations of the Chilean Government for patients with COVID-19, including household isolation. Within each household, the index case will be asked to isolate from their contacts.

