All adverse events/serious adverse events will have their relationship to the trial intervention and severity assessed by the investigator who evaluates the adverse event, based on temporal relationship and his/her clinical judgment. All severe adverse events will be reported immediately to the sponsor, except for those SAEs that are identified as not requiring immediate reporting. The immediate reports should be followed promptly by detailed, written reports. Clinic trial liability insurance will cover costs for participants who suffer harm during trial participation. Investigators will ensure harmed participants receive treatment for their condition.

IFN treatment is known to induce injection site erythema and, in up to 80% of recipients, an ‘influenza like’ syndrome, comprising fever, headache and body aches. Importantly, there are no respiratory signs or symptoms associated with IFN treatment, i.e. the response to IFN treatment is different than COVID-19 disease. However, ‘flu-like symptoms’ also occur in COVID-19 disease, and could lead to an increase in clinical tests in the IFN treated cohort if not appropriately managed. There are several strategies that may mitigate this potential response to IFN treatment that already constitute standard practice for multiple sclerosis (MS) patients on IFN therapy. Participants will be informed about the likely side effects of IFN treatment and asked to monitor and manage these. Monitoring consists of self-assessment of symptoms (there are no respiratory symptoms or anosmia known to be associated with IFN use) and the time frame during which this ‘influenza like’ syndrome following IFN treatment occurs (restricted to the first 4–24 h after administration of an IFN dose). Management consists of advising the participant to take acetaminnophen (provided to the participant) from the time of IFN administration up to 24 h after, to reduce the likelihood of this ‘influenza like’ syndrome. This approach is recommended for individuals with MS receiving IFN therapy (see PLEGRIDY package insert product monograph) and reduces syndrome symptoms by 80%.

Interferon ß-1a is safe when taken during pregnancy, with no evidence of increased rates of congenital anomalies or spontaneous abortions, according to data reported by the European IFNbeta Pregnancy Registry. If a female subject is diagnosed as pregnant by a positive.

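### The control arm's single acetaminophen course cannot match the interferon arm's three, and the amount around each injection can be read two ways

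*Protocol article*

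**What the plan says.** All places are in the protocol article.

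- **Baseline and follow-up home visits, text, IFN arm.** Participants are advised to "take the provided acetaminophen (1000 mg 4 times per day) from the time of IFN administration until 24 h post-injection".
- **Same paragraph, control arm.** Participants are "instructed to take the provided acetaminophen within 24 h of the first home visit, to conform with the intervention group". No amount or number of doses is given, and no later visit is mentioned.
- **Table 2, days 1, 6 and 11.** Each visit lists "Administer acetaminophen 1000 mg PO pre-medication, if applicable" directly before study drug administration.
- **Intervention arm.** The drug is "administered on Study Days 1, 6 and 11 (i.e. for a total of 3 doses". This section describes those treated as index cases and treatment-eligible household contacts.
- **Data and safety monitoring.** The same advice appears again, "from the time of IFN administration up to 24 h after, to reduce the likelihood of this" syndrome, without an amount and without mention of the pre-medication.
- **Control arm.** Standard of care is symptom-based and comes from the participant's own provider: "This could include acetaminophen, non-steroidal anti-inflammatory drugs" and other drugs.

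**The concern.** The article gives a purpose for the control-arm acetaminophen, which is to make the arms alike, and then a schedule that cannot achieve it beyond the first visit. A reader who relies on the stated purpose would take the arms to be alike in antipyretic and analgesic use throughout dosing.

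The article itself says that this exposure matters for symptoms. Data and safety monitoring reports an influenza-like syndrome in up to 80% of IFN recipients, says the acetaminophen approach reduces its symptoms by 80%, and warns that the overlap with COVID-19 symptoms could lead to more clinical testing in treated participants. Participants in both arms record symptoms in a diary, participants and staff are unblinded, and safety is a secondary objective. After the day 6 and day 11 visits, scheduled acetaminophen in one arm is compared with as-needed use in the other.

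The second strand concerns the participants directly. Two instructions on the amount taken around an injection stand side by side, and field teams could apply them differently.

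**Working it through.** The plan states no total and no power figure that depends on this point, so there is nothing to reproduce. The check is a count and simple sums.

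**Courses instructed**

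| Visit | IFN arm | Control arm |
|---|---|---|
| Day 1 | 24 h course after injection | course within 24 h of the visit, amount not stated |
| Day 6 | 24 h course after injection | none instructed |
| Day 11 | 24 h course after injection | none instructed |
| Total | 3 | 1 |

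Two entries might seem to fill the control column. The Table 2 pre-medication carries a proviso that it applies where applicable, and it precedes a study drug that controls never receive, so it does not clearly extend to them. Acetaminophen from a participant's own provider is taken for symptoms and is not a scheduled course.

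**Amount around one injection, IFN arm** (assuming four doses in the 24 h window)

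- Pre-medication counted as one of the four: 4 × 1000 mg = 4000 mg.
- Pre-medication additional: 1000 mg + 4 × 1000 mg = 5000 mg.
- Ratio: 5000 / 4000 = 1.25, so the second reading is 25% higher.

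**Over three injections**

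- 3 × 4000 mg = 12,000 mg, or 3 × 5000 mg = 15,000 mg.

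**Control arm**

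- No total can be computed because no amount is stated. If the four-times-daily regimen is assumed, the instructed course is 4000 mg, once. That is an assumption and not an upper limit, since provider-supplied acetaminophen is also possible.

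**Which outcomes are exposed**

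- Table 2 specifies that vital signs on days 6 and 11 are taken before study drug. The previous 24 h window closed about four days before (day 2 to day 6, day 7 to day 11). Staff-measured temperature at those visits is therefore not directly affected.
- Diary symptoms and adverse events in the roughly 24 h after the day 6 and day 11 visits fall inside the IFN-arm window, with no instructed counterpart in control.
- The co-primary outcomes are RT-PCR results at day 11. The documents give no route from acetaminophen to these.

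**The case against.** The case for leaving the text alone has several parts.

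*The two amounts are compatible.* The pre-medication is given at about the moment the four-times-daily advice begins, so it can be read as the first of the four doses. This stands in part. A reader might call the 4000 and 5000 mg readings a contradiction, but the documents support only an ambiguity. The ambiguity remains because no section settles it, and both instructions are stated in the article itself.

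*Acetaminophen is part of the IFN package.* In an open-label trial without placebo, prophylaxis for a known drug effect belongs to the treatment being compared. That is a legitimate comparison, but it is not the one the article describes when it says the control instruction exists to make the arms alike.

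*The harm is not quantified.* This is correct. Milligrams of instructed drug are not an estimate of bias, and the documents give no basis for one.

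Two stronger readings are tempting and should not be drawn:

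- A reader might add provider-supplied acetaminophen to the IFN-arm total. The passage that mentions it describes control-arm care only, so the sources are not shown to combine in one participant.
- A reader might infer that control households' treatment-ineligible contacts, defined in Table 1 as "Under 18 years OR ≥ 80 years of age OR aged 18 to < 80 years with any contraindication for IFN treatment", are directed to take it. The sentence does address control-arm participants without qualification. But its stated purpose is to mirror the intervention group, which the Intervention arm section limits to index cases and treatment-eligible contacts. What remains is a gap in wording.

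**Conclusion.** The point holds in two limited parts. First, the conformity statement fails after day 1: three instructed courses in the IFN arm against one in control, on the article's own schedule. Second, the IFN-arm amount around each injection has two readings, 4000 mg or 5000 mg, and the later description under Data and safety monitoring does not resolve them.

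The count of courses needs no assumption beyond the stated visit days. The milligram figures assume four doses per 24 h window. Any control-arm total rests on an amount the article does not give.

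The reach is the open-label comparison of diary-recorded flu-like symptoms, tolerability and adverse events after the day 6 and day 11 visits, together with participant safety. The point should be corrected, but it does not threaten the co-primary analyses or the sample size.

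**What to change.** 1. Reconcile Baseline and follow-up home visits (text and Table 2), Intervention arm, and Data and safety monitoring. Afterwards the conformity statement should agree with the schedule or be withdrawn, the 24 h total should have one reading, and it should be clear which control-arm participants are covered. The amount, the schedule and the participants covered are for the sponsor to decide.
2. Report acetaminophen use by arm beside the symptom and tolerability results. The source is the concomitant-medication record, which Table 2 already has documented on day 1 and reviewed on days 6, 11 and 29. This assumes that the acetaminophen supplied by the trial is entered there.
3. Do not describe the arms as matched on acetaminophen after day 1.

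The cost is a short text amendment and one table. Trial status gives 251 households enrolled of a planned 310 (251 / 310 = 81%), so a wording change would reach at most the remaining 59 in full. If it altered what controls are told, it would leave two instruction periods within that arm. The reporting step is the part that covers every household.
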